**Participant timeline**

The participants will be asked to complete the questionnaires personally at baseline, after 3 months of treatment, at 6-month follow-up, and at 12-month follow-up. During the follow-up period, the experimental team will contact the participants either via Wechat or phone regularly so that the data at the 6- and 12-month time points can be collected. Table 2 displays the items of the questionnaire and the measurement time points.

**Sample size calculation**

Sample size was calculated by G*power 3.1.9 based on the following conditions. According to Costantino's trial, the subjects of the two groups received 12 weeks of aquatic exercise and back school program respectively. The effect size was calculated to be 0.35 by using the RMDQ score of the experimental group (mean = 5.37, SD = 1.82) and the control group (mean = 6.11, SD = 2.36) during the 3-month follow-up.(Costantino & Romiti, 2014) The two groups were measured 4 times by using a mixed design of repeated measures analysis of variance. Considering that α = 0.05, power (1-β) = 0.95, Corr amongst rep measures = 0.5, the total sample size was 70. Considering the possibility of a 20% missing rate, the minimum sample size was 88. According to the calculation, 100 subjects will be expected to be recruited, and 50 subjects will be included in each group.

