**Study design**

This study is a 3-month single-blind RCT with a 12-month follow-up (Trial registration: ChiCTR1800016396). All included participants will be randomly allocated into either the TAE group or the PTMs group. The interventions of two groups will be carried out in Shangti indoor constant temperature swimming pool and Shanghai Shangti Orthopeadics Hospital respectively. Experienced physiotherapists will carry out the measurements at baseline, after the 3-month intervention, at 6-month follow-up, and at 12-month follow-up from the beginning to determine whether short-term effects and long-term impacts will be achieved.

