**Randomization and blinding**

Randomization in a 1:1 ratio will be performed according to a computer-generated scheme, and participants will be assigned into the control group (PTMs) or the experimental group (TAE). A researcher who carries out the randomization with sealed and opaque envelopes will remain separated from the intervention team.

A group of assessors will be responsible for each block of the measurement, but they are not aware of the group assignments and remain distant from the invention. The instructors are masked to the study’s hypothesis and experimental purpose. To be ignorant of grouping when receiving a behavior-related treatment at the mean time is impossible for participants.

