**Statistical analysis**

Data will be collected and analyzed via SPSS 20.0 and Microsoft 2016. Considering that someone may drop out midway, all outcomes should be conducted by intention-to-treat analysis and per-protocol analysis. For baseline variables, we will detect the categorical variables (e.g. gender, education levels and occupation) with chi-square test and analyze the continuous variables (e.g. age, height, weight, BMI, and pain intensity) with independent t-test or Mann–Whitney U test to compare the statistical significance between the TAE group and the PTMs group. The results of descriptive statistics will be presented as mean ± standard deviation.

The experimental results were compared through adjusted two-way repeated measures ANOVA (group × time). The adjustment factors included gender, age, BMI, physical activity, LBP duration, NRS of the most severe LBP, medication, and smoking history. A chi-square test was conducted to compare the proportion of participants in each group who met the MCID for pain and function at postintervention. Although the MCID for RMDQ and NRS remains controversial, values of 5.0 and 2.0 are considered reasonable and commonly used. The χ2 test was also applied to determine the difference between the 2 groups for the proportion of participants reporting GPE, adverse events and treatment recommendations. The effect sizes were presented to measure the strength of any outcome indicators, where 0.2 ≤ Cohen’s d < 0.5 means a ‘small’ effect size, 0.5 ≤ Cohen’s d < 0.8 indicates a ‘medium’ effect size and Cohen’s d ≥ 0.8 reflects a ‘large’ effect size.

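### The total of 70 matches a power routine for the group difference averaged over four visits, baseline included, so the stated 95% is not the power of the planned group × time comparison

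*Protocol*

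**What the plan says.** In the Protocol, Sample size calculation, the effect size comes from the RMDQ results of an earlier trial at its 3-month follow-up: "The effect size was calculated to be 0.35 by using the RMDQ score". The summary figures given for that trial's two arms are "the experimental group (mean = 5.37, SD = 1.82) and the control group (mean = 6.11, SD = 2.36". The design entered is described as follows: "The two groups were measured 4 times by using a mixed design of repeated measures analysis of variance". The result is: "Considering that α = 0.05, power (1-β) = 0.95, Corr amongst rep measures = 0.5, the total sample size was 70". An allowance of 20% for missing data raises this to 88, and 100 are to be recruited, 50 per group.

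Study design fixes the four occasions: "Experienced physiotherapists will carry out the measurements at baseline, after the 3-month intervention, at 6-month follow-up, and at 12-month follow-up". Participant timeline and Table 3 agree. Allocation is random: "Randomization in a 1:1 ratio will be performed according to a computer-generated scheme". The analysis in Statistical analysis is: "The experimental results were compared through adjusted two-way repeated measures ANOVA (group × time", adjusted for eight covariates.

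The paragraph does not say which G*Power routine was run, or whether the group effect or the interaction is being powered.

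**The concern.** A two-group repeated-measures ANOVA yields a group main effect (the difference averaged over visits) and a group × time interaction (whether the difference changes over visits). They have different power under the same pattern of differences. The printed total fits a calculation for the main effect, while the analysis section points to the interaction.

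The baseline visit makes this matter. Randomised groups have an expected baseline difference of zero, and the source difference is a follow-up value. It can therefore apply to at most three of the four visits. Counting baseline as a fourth visit that carries the full average difference overstates power for the main effect. It also says nothing about the interaction: if the difference were equal at all four visits, the interaction would be exactly zero and its power would equal α, 5%.

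At stake is how the primary result is read. A null RMDQ finding would be judged as coming from a test with 95% power, and the 70, 88 and 100 all rest on that figure.

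**Working it through.** **Inputs** (Protocol, Sample size calculation): effect size 0.35; m = 4 measurements; ρ = 0.5; α = 0.05; power 0.95; RMDQ 5.37 (SD 1.82) against 6.11 (SD 2.36). The visits are baseline, 3, 6 and 12 months. All power figures are from the noncentral F distribution, assuming sphericity and no gain from covariates.

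**1. Reproducing 70.** Between-factors routine: λ = f²·N·m / (1 + (m−1)ρ), with df 1 and N−2.
- f = 0.35, N = 70: λ = 0.1225 × 70 × 4 / 2.5 = 13.72, power 0.955. N = 68 gives 0.949, so 70 is the smallest equal-group total.
- 70 / 0.8 = 87.5, rounded up to 88, as printed.

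Within-between interaction routine: λ = f²·N·m / (1−ρ), with df 3 and 3(N−2).
- f = 0.35 gives N = 20 (power 0.961).
- f = 0.175 gives N = 72 (power 0.952). This is close, but it needs an entry other than the printed 0.35 and does not give 70.

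**2. What the matching routine assumes.** For two equal groups f = d/2, so f = 0.35 is a difference of 0.70 SD, averaged over the four visits. With zero at baseline, the three later visits would have to average 0.70 × 4/3 = 0.93 SD.

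**3. Power with zero at baseline and D at the three later visits.**
- Group × time: λ = (N/4)·Σ(Dj − mean)² / (1−ρ), df 3 and 3(N−2).
- Group main effect: λ = (N/4)·(0.75D)² / ((1+3ρ)/4), df 1 and N−2.

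For D = 0.70 and N = 70 the mean is 0.525. The sum of squares is 0.525² + 3 × 0.175² = 0.3675. The interaction λ is 17.5 × 0.3675 / 0.5 = 12.86, and the main-effect λ is 17.5 × 0.2756 / 0.625 = 7.72.

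| 0.35 accepted as entered (D = 0.70 SD) | N = 70 | N = 80 | N = 100 |
| --- | --- | --- | --- |
| Between-factors routine, 0.70 SD average over four visits | 0.955 | 0.974 | 0.992 |
| Group × time, zero at baseline | 0.860 | 0.906 | 0.960 |
| Group main effect, zero at baseline | 0.782 | 0.835 | 0.908 |

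Here 80 is the number left from 100 after 20% loss. For group × time, 95% needs 96 analysed.

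**4. Sensitivity.** At N = 70 and D = 0.70, group × time power is 0.71 at ρ = 0.3 and 0.98 at ρ = 0.7. If the difference halves after 3 months (0, 0.70, 0.35, 0.35) with ρ = 0.5, it is 0.68 at N = 70 and 0.84 at N = 100.

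**5. The separate scale error.** Pooled SD = √((1.82² + 2.36²)/2) = 2.107, and 0.74 / 2.107 = 0.351. The printed 0.35 is therefore Cohen's d, whereas the match in step 1 needs it entered as f. With D = 0.351:

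| D = 0.351 SD | N = 70 | N = 80 | N = 100 |
| --- | --- | --- | --- |
| Between-factors routine, f = 0.175 | 0.447 | 0.498 | 0.592 |
| Group × time, zero at baseline | 0.289 | 0.328 | 0.405 |
| Group main effect, zero at baseline | 0.279 | 0.313 | 0.378 |

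At N = 80 the scale correction alone takes the between-factors figure from 0.974 to 0.498. Moving to group × time with zero at baseline takes it on to 0.328.

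**6. Detectable difference.** With 80 completers and ρ = 0.5, group × time has 80% power at D = 0.61 SD (0.61 × 2.107 ≈ 1.3 RMDQ points) and 95% at 0.76 SD (about 1.6 points). The source difference is 0.74 points.

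**The case against.** The strongest objection is that the routine is inferred. The Protocol names none, and the interaction routine with f = 0.175 comes within two patients of 70. This stands as a limit: one can say that 70 is reproduced by the between-factors routine, not that the Protocol reports using it. The exact match with every printed input still makes it the better reading, since the rival needs an effect size that is not printed.

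A reader might go further and infer that the plan assumes a treatment effect before treatment. The documents do not support that. The routine needs only a four-visit average, and a constant difference from baseline onward is just one pattern with that average. The sound statement is that a zero baseline dilutes the average.

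It may also be said that group × time only describes the layout, and that the group main effect is the intended test. That effect is a standard output of the analysis, but its power is lower: 78% at 70 and 83% at 80.

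Nor does the interaction routine's N = 20 show that 70 is generous. An interaction f of 0.35 with zero at baseline and equal later differences implies about 1.62 SD, or 3.4 RMDQ points, against a source difference of 0.74.

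Finally, the isolated loss is modest, and the eight covariates could recover some of it. Both points stand and limit how much weight the finding carries.

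**Conclusion.** The point holds in a limited form. On either reading of the planned analysis, 70 patients do not give the stated 95% power once the randomised baseline is set to zero. With 0.35 accepted as entered, the isolated shortfall at 70 is about 9 points for group × time and 17 for the main effect. At 80 completers group × time has 91%, and if all 100 are analysed it reaches 96%. These figures rest on a difference sustained from 3 to 12 months, ρ = 0.5, sphericity and no covariate gain; a lower correlation or a fading effect makes them worse, and a higher correlation makes the group × time figure better.

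A reader might infer that this error alone leaves the trial with 29% to 40% power. It does not. Those figures also require correcting the d-for-f substitution, which accounts for most of the fall and is a separate point.

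**What to change.** Keep the recruitment target of 100. In Sample size calculation, name the test being powered so that it agrees with Statistical analysis. Restate its power with a zero RMDQ difference at baseline and the source difference at post-baseline visits only, and give the correlation and the pattern over time that are assumed. If the effect-size scale is corrected in the same edit, the group × time figure is about 33% at 80 completers, and the text should make clear that most of the change comes from the scale.

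Alternatively, state what 80 completers can detect with that test: about 0.61 SD (1.3 RMDQ points) at 80% power, or about 0.76 SD (1.6 points) at 95%, beside the 0.74-point source difference.

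The cost is rewording one paragraph, with no extra patients or visits. The downside is a less favourable stated power.

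### The sample size appears to use Cohen's d = 0.35 as Cohen's f, so the stated 95% power does not hold for the 0.74-point RMDQ difference it was derived from

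*Protocol*

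**What the plan says.** The section on sample size calculation in the protocol uses G*Power 3.1.9 and takes its planning values from a cited trial of aquatic exercise against a back school programme. It states: "The effect size was calculated to be 0.35 by using the RMDQ score". The values are RMDQ results for the "experimental group (mean = 5.37, SD = 1.82") and for "the control group (mean = 6.11, SD = 2.36) during the 3-month follow-up". The test family is given as: "The two groups were measured 4 times by using a mixed design of repeated measures analysis of variance". The result is: "Considering that α = 0.05, power (1-β) = 0.95, Corr amongst rep measures = 0.5, the total sample size was 70". The allowance for loss follows: "Considering the possibility of a 20% missing rate, the minimum sample size was 88". The recruitment target is then set at 100, 50 per group.

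The section names neither the effect-size metric (d or f) nor the G*Power option (between factors, within factors or interaction). The statistical analysis section plans an adjusted two-way repeated-measures ANOVA of group by time. It grades reported effects on the d scale, for example "0.2 ≤ Cohen’s d < 0.5 means a ‘small’ effect size". That concerns how results will be described and does not show what was entered in the software.

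**The concern.** A standardised difference between two means is Cohen's d. The ANOVA modules of G*Power expect Cohen's f, which is half of d when two groups are of equal size. Entering d as f doubles the assumed effect and makes the required sample about four times too small. The stated inputs (means, SDs, correlation, four measurements) and the stated output (70 in total for 95% power) would then contradict each other.

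RMDQ is the primary outcome, and the hypotheses predict significant differences both after treatment and during follow-up. A reader who trusts 95% power would take a non-significant result as good evidence against a difference of the planned size, when the trial would more often than not miss such a difference with the planned test.

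**Working it through.** **Inputs.** From the sample size section: means 5.37 and 6.11; SDs 1.82 and 2.36; α = 0.05; power 0.95; correlation ρ = 0.5; m = 4 measurements; 20% loss. From the randomisation section: 1:1 allocation. No sphericity correction is applied, as the protocol states none.

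**Step 1: which metric is 0.35?**
- Pooled SD = √((1.82² + 2.36²)/2) = 2.107.
- d = (6.11 − 5.37)/2.107 = 0.74/2.107 = 0.351.
- f = d/2 = 0.1756, or 0.175 from the rounded 0.35.

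The stated 0.35 is therefore d.

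**Step 2: reproduce the 70.** Noncentral F distribution:
- Between factors: λ = f²·N·m/(1 + (m − 1)ρ) = 1.6·f²·N, with df 1 and N − 2.
- Interaction: λ = f²·N·m/(1 − ρ) = 8·f²·N, with df 3 and 3(N − 2).

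| f entered | Option | Smallest even N for 95% power |
|---|---|---|
| 0.35 | between factors | **70** (0.949 at 68, 0.955 at 70) |
| 0.35 | within or interaction | 20 |
| 0.175 | between factors | 268 |
| 0.175 | within or interaction | 72 (0.946 at 70) |

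Only f = 0.35 between factors returns 70. The loss step is correct: 70/0.8 = 87.5, rounded up to 88.

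**Step 3: what f = 0.35 means.** d = 2 × 0.35 = 0.70, and 0.70 × 2.107 = 1.48 RMDQ points, against 0.74 in the cited data.

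**Step 4: same settings with f = 0.175.**

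| N | λ = 1.6 × 0.175² × N | Power |
|---|---|---|
| 70 | 3.43 | 44.7% |
| 80 (100 less 20%) | 3.92 | 49.8% |
| 88 | 4.31 | 53.7% |
| 100 | 4.90 | 59.2% |

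**Step 5: allow for equal groups at baseline.** The between-factors test averages all four visits, baseline included, so step 4 assumes a 0.35 SD difference before treatment starts. Assume instead standardised differences of (0, 0.351, 0.351, 0.351).
- Between factors: the mean difference is 0.75 × 0.351 = 0.263, so f = 0.132. Power is 28% at 70, 31% at 80 and 38% at 100.
- Group × time: the half-differences, centred over visits, are −0.1316 once and +0.0439 three times. So f = √((0.1316² + 3 × 0.0439²)/4) = 0.076. At N = 80, λ = 8 × 0.076² × 80 = 3.70 and power is 33%. At N = 100, λ = 4.62 and power is 40%. At N = 70, power is 29%.

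**The case against.** The strongest objection is that the substitution is inferred. The protocol names neither metric nor option, and f = 0.175 in the interaction option, which matches the planned analysis, gives 72, close to 70. An f of 0.177 to 0.178 there would give exactly 70. This stands as a reason to write that d *appears* to have been used as f. It does not displace the reading: the stated value is 0.35, d/2 from the cited figures is 0.1756, and that value still gives 72. Nor would it rescue the power, because d/2 at a single visit is not an interaction effect size. Under the pattern in step 5 the interaction f is 0.076.

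A reader might infer that the trial's true power is simply 45–50%. The documents do not support that. The range is what the same menu setting gives at 70 to 80 participants. The protocol recruits 100 and plans intention-to-treat analysis, for which the same setting gives 59%. All these figures carry the baseline assumption just described, and they belong to a test other than group × time.

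Two further points stand as limits. The analysis adjusts for eight factors, which may add power, but the protocol gives no figures from which to estimate the gain. And 0.74 points is only about one-seventh of the 5-point MCID that the protocol adopts for RMDQ. Low power for 0.74 points therefore does not mean that the trial could miss a difference of 5 points. The error lies in the power claimed for the protocol's own planning difference.

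**Conclusion.** The point holds in this form. The planning effect of 0.35 is d, the total of 70 matches its use as f, and 95% power for a 0.74-point RMDQ difference is wrong as stated. With f = 0.175 the protocol's apparent settings give about 45% at 70, 50% at 80 and 59% at 100. They would need 268 for 95%, nearly four times 70.

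For the planned group × time test, power is about 33% at 80 and 40% at 100. This assumes equal groups at baseline, d = 0.35 at all three later visits, a common correlation of 0.5, and no gain from covariates.

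The conclusion rests on the protocol's own means, SDs and correlation and on the standard G*Power formulas. The cause is a strong inference; the mismatch between the cited difference and the claimed power under the settings that reproduce 70 is arithmetic. It does not follow that the trial must recruit 268.

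**What to change.** Keep the 100 participants and rewrite the sample size paragraph:

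- Name the metric and the G*Power option used. State that the cited data give d = 0.35, hence f = 0.175 for two equal groups.
- Withdraw the claim of 95% power for a 0.74-point difference.
- Restate power for the planned group × time test together with its assumed visit pattern: about 33% with 80 participants and 40% with 100, if the groups are equal at baseline and differ by 0.35 SD at each later visit, without counting any covariate gain.
- State that 70 participants (88 with 20% loss) give 95% power only for a difference of about 0.70 SD, or 1.5 RMDQ points, under the between-factors settings used, which take that difference as the average over all four visits.

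The cost is the rewording of one paragraph, with no extra participants and no change to the analysis. The downside is that the stated power becomes much less favourable.

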**Statistical analysis**

Data will be collected and analyzed via SPSS 20.0 and Microsoft 2016. Considering that someone may drop out midway, all outcomes should be conducted by intention-to-treat analysis and per-protocol analysis. For baseline variables, we will detect the categorical variables (e.g. gender, education levels and occupation) with chi-square test and analyze the continuous variables (e.g. age, height, weight, BMI, and pain intensity) with independent t-test or Mann–Whitney U test to compare the statistical significance between the TAE group and the PTMs group. The results of descriptive statistics will be presented as mean ± standard deviation.

The experimental results were compared through adjusted two-way repeated measures ANOVA (group × time). The adjustment factors included gender, age, BMI, physical activity, LBP duration, NRS of the most severe LBP, medication, and smoking history. A chi-square test was conducted to compare the proportion of participants in each group who met the MCID for pain and function at postintervention. Although the MCID for RMDQ and NRS remains controversial, values of 5.0 and 2.0 are considered reasonable and commonly used. The χ2 test was also applied to determine the difference between the 2 groups for the proportion of participants reporting GPE, adverse events and treatment recommendations. The effect sizes were presented to measure the strength of any outcome indicators, where 0.2 ≤ Cohen’s d < 0.5 means a ‘small’ effect size, 0.5 ≤ Cohen’s d < 0.8 indicates a ‘medium’ effect size and Cohen’s d ≥ 0.8 reflects a ‘large’ effect size.

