**Withdrawal criteria**

1. Patients lose interest; 2. Patients’ schedule conflict with the experimental arrangement; 3. Patients develop serious conditions, such as stroke; 4. Patients experience a side effect due to TAE or PTMs.

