**Interventions**

The intervention sessions will be carried out by a group of qualified physicotherapists who will not take part in the data collection. Both programs will last 12 weeks and will be administered twice per week for a total of 24 treatment sessions. The participants will be encouraged to complete the intervention as designed, and the adherence rate is expected to be at least 75%. Attendance frequency, medication changes, and adverse events during the sessions and after treatment will be filled out in a daily record form. Once a participant absents from the intervention sessions, he or she will be contacted immediately to determine the reason. Participants who withdraw halfway, fail to attend the evaluations, or miss more than 2 weeks will be regarded as drop-outs (Li et al., 2012).

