
10. The participants’ overall assessment of the treatment was measured on the basis of the global perceived effect (GPE). The GPE scale requires patients to rate how much they have improved or deteriorated since they received the treatment. The use of this scale is widely advocated in pain research because it is easy and quick to understand and score, and its results are important to patients.(Evans, Bronfort, Maiers, Schulz, & Hartvigsen, 2014) The most meaningful changes can be observed in patients answering the scale at a predefined time point. The GPE scale has excellent reproducibility (ICC = 0.90–0.99), and its correlation with disability (r = 0.40–0.74) is strong.(Kamper et al., 2010)

11. Adverse events were collected from participants’ daily record forms. All pain (LBP or other pain) related to intervention or unrelated to intervention occurring during the research duration was considered.

12. The participants’ recommendation levels on the intervention that they received were classified as highly recommended, recommend, unclear, not recommended and strongly deprecated.

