| The Minimal Clinically Important Difference (MCID) |  | ✖ | ✖ | ✖ |
| Global Perceived Effect (GPE) |  | ✖ | ✖ | ✖ |
| Adverse Events |  | ✖ | ✖ | ✖ |
| Recommendation |  | ✖ | ✖ | ✖ |

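### The per-protocol comparison of adverse events, ordered alongside intention-to-treat, leaves out participants withdrawn because of treatment-related harm

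*Protocol*

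**What the plan says.** Four parts of the protocol bear on this point.

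- **Statistical analysis.** The stated reason for using two analyses is drop-out ("Considering that someone may drop out midway"). The instruction that follows is that "all outcomes should be conducted by intention-to-treat analysis and per-protocol analysis". The same section applies a chi-square test to the proportion of participants with adverse events.
- **Secondary outcomes, item 11.** "Adverse events were collected from participants’ daily record forms". The scope is wide: "All pain (LBP or other pain) related to intervention or unrelated to intervention occurring during the research duration was considered".
- **Withdrawal criteria, item 4.** "Patients experience a side effect due to TAE or PTMs". No severity threshold is attached.
- **Interventions.** "Participants who withdraw halfway, fail to attend the evaluations, or miss more than 2 weeks will be regarded as drop-outs".

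Adverse events are therefore a numbered outcome with a planned between-group test, and the instruction to analyse every outcome both ways covers them.

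**The concern.** A per-protocol set is meant to show the effect of treatment in those who followed the plan. For efficacy outcomes that is a familiar supplement to intention-to-treat. For adverse events it is circular when harm is itself a reason for leaving. Staying in the set then depends partly on not having had a treatment-related event that led to withdrawal, so the comparison is selected on the outcome it measures.

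The arms need not cause similar harm. One is exercise at a target perceived exertion of about 13; the other is passive electrical stimulation and infrared heat. Because pain of any kind counts as an adverse event, pain attributed to treatment can be both a counted event and a reason for withdrawal. The protocol does not say which of the two analyses leads. A reassuring per-protocol safety result could therefore stand beside the sound one as if it carried equal weight.

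**Working it through.** **Inputs.** From the protocol: 50 participants per arm (Sample size calculation), a chi-square test on the proportion with adverse events, and the withdrawal and drop-out rules above. The protocol gives no adverse-event rate and no figure for this comparison, so there is nothing of its own to reproduce. All event rates below are assumptions. The per-protocol set is taken to exclude drop-outs.

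**Step 1: related events only.** Let p be the true proportion in an arm with an intervention-related event, and w the fraction of those who are withdrawn for it. Then

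per-protocol rate = p(1 − w) / (1 − pw).

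For 0 < p < 1 and w > 0 this is always below p, so each arm's rate is understated whatever the true values.

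Assume p = 20% in one arm and 6% in the other, with w = 0.5 in both:

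- 0.20 × 0.5 / (1 − 0.10) = 0.10 / 0.90 = 11.1%
- 0.06 × 0.5 / (1 − 0.03) = 0.03 / 0.97 = 3.1%

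The difference falls from 14 to 8 points. In all randomised participants the same rates are 10/50 v 3/50, with uncorrected chi-square (10 × 47 − 3 × 40)² × 100 / (50 × 50 × 13 × 87) = 4.33, p about 0.04.

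**Step 2: direction.** The shrinkage in step 1 uses the same w in both arms. Take p = 20% in both arms with w = 0.8 and 0.2:

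- 0.20 × 0.2 / (1 − 0.16) = 0.04 / 0.84 = 4.8%
- 0.20 × 0.8 / (1 − 0.04) = 0.16 / 0.96 = 16.7%

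Here a difference is created where none exists. The rates are always too low, but the error in the difference can go either way.

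**Step 3: the outcome as the protocol defines it.** Unrelated pain also counts and does not trigger the side-effect criterion. Assume 5 further participants per arm with unrelated events only, and aquatic exercise (TAE) v physical therapy modalities (PTMs) at 50 per arm:

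| Related cases, TAE v PTMs | Fraction withdrawn | All randomised | Per-protocol |
| --- | --- | --- | --- |
| 10 v 2 | half | 15/50 (30%) v 7/50 (14%), p = 0.053 | 10/45 (22.2%) v 6/49 (12.2%), p = 0.20 |
| 10 v 2 | all | 15/50 (30%) v 7/50 (14%), p = 0.053 | 5/40 (12.5%) v 5/48 (10.4%), p = 0.76 |
| 5 v 1 | all | 10/50 (20%) v 6/50 (12%) | 5/45 (11.1%) v 5/49 (10.2%) |
| 15 v 3 | all | 20/50 (40%) v 8/50 (16%) | 5/35 (14.3%) v 5/47 (10.6%) |

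If all related cases are withdrawn, differences of 8, 16 and 24 points become about 1, 2 and 4. If half are withdrawn in the 10 v 2 case, 16 points become 10.

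**The case against.** The strongest reply is that intention-to-treat is ordered in the same sentence and keeps withdrawn participants in their assigned arm. That is right, and it limits the point. A reader might infer that adverse events are compared only per-protocol, or that harmed participants disappear from the trial's safety results. The text supports neither: they are lost from one of two comparisons.

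Second, the per-protocol set is not defined, and its definition may stand in a statistical analysis plan that is not shown. This also stands: the exclusion of drop-outs is inferred from the stated reason for the two analyses and the usual meaning of the term. The complaint, however, is about an instruction the protocol does give. An analysis plan that exempted adverse events would depart from that instruction.

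Three stronger readings are tempting and should be resisted.

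- *The per-protocol event rate would be zero in both arms.* This holds only for related events, and only if every participant with a side effect is withdrawn. The criterion stands beside loss of interest and schedule conflicts, so it can be read as a list of reasons for leaving rather than a rule to remove everyone affected. Unrelated pain is counted as well, so events would remain.
- *The bias always runs towards no difference.* Step 2 shows that it need not.
- *Table 3 loses early events because its first adverse-event entry is at 3 months.* Events are taken from daily record forms, which cover the sessions and the time after treatment. An event in an early week is recorded when it occurs, and the protocol describes no adverse-event table confined to visit attenders.

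**Conclusion.** The point holds for the per-protocol adverse-event comparison and for that comparison only. As instructed, it leaves out participants withdrawn because of treatment-related harm, understates intervention-related event rates in each arm, and can shrink or distort the between-arm difference according to how often harmed participants are withdrawn in each arm. The conclusion rests on one inference, that the per-protocol set excludes drop-outs. The direction of the error in each arm's rate follows from the formula; its size cannot be fixed from the protocol. The worked figures show only that it could be material at 50 per arm. Because a sound comparison is already ordered, this is a worthwhile correction to the analysis text and not a threat to the trial's safety data.

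**What to change.** In the Statistical analysis section, restrict per-protocol analysis to efficacy outcomes. State that adverse events are compared in all randomised participants by assigned group, counting every event on the daily record forms up to and including any that led to withdrawal. List withdrawals for side effects by arm next to that comparison. The assigned-group comparison need not be replaced by an as-treated one, and nothing here asks for a change to the withdrawal criteria.

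The cost is a sentence or two of text and no new data. The downside is one fewer per-protocol table and a safety result that may look less favourable.
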